| Study Population:                                                                              | Overweight/obese participants with MetS who are consuming $\geq 1$ SSBs/day                                                                                                                                                                                                                                                                                                                                                                                                                                                                                                                                                                                                                                                                                                                                                                                                                                                                                                                                                                                                                                                                                                                                           |

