## 4. STUDY DESIGN

### 4.1. Overall Design

The trial will be conducted at the MRI Research Unit and at the Clinical Nutrition and Risk Factor Modification Centre at St. Michael's Hospital. The trial will be a 24-week, 2-phase, 3-arm, non-inferiority, open-label, parallel group, randomized controlled trial to assess the effect of replacing SSBs with 2% soy milk versus 2% cow's milk on the primary outcome liver fat and secondary outcomes muscle fat, insulin sensitivity, beta-cell function, glucose tolerance and established cardiometabolic risk factors in overweight/obese participants who are consuming  $\geq 1$  SSBs/day (see Figure 1). The trial will be conducted according to Good Clinical Practice and reported according to CONSORT and the COSORT extension for non-inferiority trials [44].

All participants will be expected to participate in the study for 28 weeks (one run-in phase of four weeks, and 24-week intervention period) and be able to attend all study visits. After randomization, all study beverages will be provided with the instruction to replace usual SSBs intake while maintaining background diets.

SSBs will be defined as any sugar-sweetened beverage (sodas and soft drinks) that contains at least 50 kcal per 8-oz serving. For the purpose of the study, SSBs will include sports/energy drinks, sweetened iced tea, homemade SSBs such as frescas or fruit drinks, but will NOT include coffee or 100% fruit juice.

[figure not shown]

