### **5. STUDY POPULATION**

#### **5.1. Inclusion Criteria**

In order to be eligible to participate in this study, an individual must meet all of the following criteria:

- Adults (age 18-75 years), men and non-pregnant women
- Overweight or obese (BMI  $\geq 25\text{kg/m}^2$ )
- High waist circumference (USA/Canada  $\geq 102\text{cm}$  in men,  $\geq 88\text{cm}$  in women; Euroid/Caucasian/Middle East, Mediterranean/Sub-Saharan African  $\geq 94\text{cm}$  in men,  $\geq 80\text{cm}$  in women)

women; and Asian [including Japanese]/Ethnic Central and South American  $\geq 90$ cm in men,  $\geq 80$ cm in women[37], with a waist diameter  $\leq 60$  cm)

- Regularly drinking SSBs ( $\geq 1$  servings/day)

We will include participants consuming  $\geq 1$  SSBs servings/day, with 50% enrichment of those consuming  $\geq 3$  SSBs servings/day.

Participants must be agreeable to consume only one study beverage for the duration of the intervention. Participants that are randomized to the 2% soy milk group will be asked to substitute their regular SSB consumption with the 2% soy milk (up to a max of 6 servings/day). Similarly, participants that are randomized to the 2% cow's milk group will be asked to substitute their regular SSB consumption with the 2% cow's milk. All participants must be proficient in English to be eligible for the study. Please see exclusion criteria for a full set of exclusion criteria.

Participants must consent to have the study drinks shipped to their home address by a third-party company, who will not be informed of their participation in the study, or be agreeable to pick up study drinks from the study site at St. Michael's Hospital.

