## 5.2. Exclusion Criteria

An individual who meets any of the following criteria will be excluded from participation in this study.

- Age  $<18$  or  $>75$  years.
- BMI  $<25$ .
- Waist circumference lower than threshold[37] (USA/Canada  $<102$ cm in men,  $<88$ cm in women; Europid/Caucasian/Middle East, Mediterranean/Sub-Saharan African  $<94$ cm in men,  $<80$ cm in women; and Asian [including Japanese]/Ethnic Central and South American  $<90$ cm in men,  $<80$ cm in women) or a waist diameter  $>60$ cm.
- Uncontrolled hypertension (or systolic blood pressure  $\geq 180$  mmHg or diastolic  $\geq 110$  mmHg)
- Self-reported diabetes
- Not regularly drinking SSBs ( $<1$  serving per day)
- Self-reported cow's milk or soy intolerance or allergy
- Self-reported pregnant or breast-feeding females, or women planning on becoming pregnant throughout the study period
- Self-reported weight loss of  $\geq 10\%$  in the last 6 months
- Complementary or alternative medicine (CAM) use as deemed inappropriate by investigators
- Self-reported Wilson's disease
- Self-reported haemochromatosis
- Self-reported inborn errors of metabolism

- Self-reported lipodystrophy
- Self-reported Cushing syndrome or disease
- Self-reported gastrointestinal disease (inflammatory bowel disease or malabsorption disorder)
- Previous bariatric surgery
- Self-reported alcoholic fatty liver disease, cirrhosis, hepatocellular carcinoma, HCV, HBV, or HAV infection, or genetic causes of liver disease (Alpha-1-antitrypsin [A1A] deficiency)
- Self-reported uncontrolled hyperthyroidism or hypothyroidism
- Self-reported high risk or very high risk chronic kidney disease (CKD) (KIDIGO 2012 criteria)
- Self-reported acute or chronic infection (e.g. salmonellosis, HIV, TB)
- Self-reported chronic inflammatory conditions
- Self-reported chronic lung disease
- Self-reported chronic pancreatitis or pancreatic insufficiency
- Self-reported cystic fibrosis
- Self-reported cancer/malignancy in the last 6 months, with the exception of skin cancer
- Self-reported schizophrenia spectrum and other psychotic disorders, bipolar and related disorders, and dissociative disorders
- Self-reported severe depression
- Self-reported major surgery in the last 6 months
- Self-reported hypopituitarism
- Self-reported hypogonadism
- Self-reported substance abuse disorder (substance dependence including alcohol or recreational drugs)

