- Participation in any trials within the last 3 months or for the duration of this study
- Any condition or circumstance which would prevent you from having an MRI (e.g. pacemaker, neurostimulators, breast tissue expanders, implants, or foreign metal object in body)
- Individuals planning on making dietary or physical activity changes throughout study duration
- If self-reported medication use, it must be at a stable dose for  $\geq 6$  months.

\*Disease exclusions will be based upon self-reported diagnosis

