### 7.3. Other Pre-specified outcomes

- Ectopic muscle fat  
IMCL in calf muscles by  $^1\text{H}$ -MRS measured at weeks 0 and 24  
[Time Frame: End value at week 24]
- MetS criteria: waist circumference  
Waist circumference measured at weeks 0, 4, 8, 12, 16, 20 and 24  
[Time Frame: End value at week 24]
- MetS criteria: FPG  
Fasting plasma glucose concentration measured at weeks 0 and 24

[Time Frame: End value at week 24]

- MetS criteria: Triglycerides  
Fasting serum triglycerides concentration measured at weeks 0 and 24  
[Time Frame: End value at week 24]
- MetS criteria: HDL-C  
Fasting serum HDL cholesterol concentration measured at weeks 0 and 24  
[Time Frame: End value at week 24]
- MetS criteria: SBP  
SBP measured at weeks 0, 4, 8, 12, 16, 20 and 24  
[Time Frame: End value at week 24]
- MetS criteria: DBP  
DBP measured at weeks 0, 4, 8, 12, 16, 20 and 24  
[Time Frame: End value at week 24]
- MetS Reversion  
Reversion to <3 of 5 IDF/NHLBI/AHA/WHF/IAAS/IASO MetS criteria measured at weeks 0 and 24  
[Time Frame: End value at week 24]
- Diabetes Incidence  
Incidence of diabetes (Diabetes Canada 2018 FPG and 2h-PG [75g-OGTT], or HbA1c criteria) measured at week 24  
[Time Frame: End value at week 24]
- Body weight  
Body weight measured at weeks 0, 4, 8, 12, 16, 20 and 24  
[Time Frame: End value at week 24]
- Microbiome diversity  
Gut microbiome composition by 16S rRNA sequencing measured at weeks 0 and 24  
[Time Frame: End value at week 24]
- NAFL markers - ALT  
Serum ALT concentrations measured at weeks 0 and 24  
[Time Frame: End value at week 24]
- NAFL markers - AST  
Serum AST concentrations measured at weeks 0 and 24  
[Time Frame: End value at week 24]

- NAFL markers - GGT  
Serum GGT concentrations measured at weeks 0 and 24  
[Time Frame: End value at week 24]
- NAFL markers - ALP  
Serum ALP concentrations measured at weeks 0 and 24  
[Time Frame: End value at week 24]
- NAFL markers – FLI  
FLI measured at weeks 0 and 24  
[Time Frame: End value at week 24]
- Hepatic insulin resistance - HOMA-IR  
Homeostatic model assessment of insulin resistance (HOMA-IR) measured at weeks 0 and 24  
[Time Frame: End value at week 24]
- Uric acid  
Serum uric acid measured at weeks 0 and 24  
[Time Frame: End value at week 24]
- Established lipid targets - LDL-C  
Serum LDL-C measured at weeks 0 and 24  
[Time Frame: End value at week 24]
- Established lipid targets - non-HDL-C  
Serum non-HDL-C measured at weeks 0 and 24  

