Secondary, exploratory, and adherence outcomes will be assessed by superiority testing among the active treatment (2% soy milk), reference treatment (2% cow's milk), and control treatment (SSB). By reporting all estimated effects and confidence intervals with p-values, the necessary context is provided for a proper interpretation of the statistical evidence [<https://www.tandfonline.com/doi/full/10.1080/00031305.2016.1154108>]. If it is required for a future regulatory submission, then the secondary outcomes will be adjusted for false discovery. The approach will depend on the results of the primary outcome. If the superiority testing of the primary outcome is significant, then we will analyze the secondary outcomes using the Benjamini-Hochberg false discovery rate controlling method with a starting alpha of 0.05 to correct for false discovery [80].

The sample size was selected to allow sufficient power for this analytical approach. The primary analysis will be conducted according to the intention to treat (ITT) principle with IPW to account for any missing values. Data will be analyzed using ANCOVA models for continuous data (mean differences with 95% CIs) and logistic regression models for categorical data (odds ratio with 95% CI for MetS reversion and relative risk with 95% CI for diabetes incidence). Adjustments will be made for age, sex, NAFLD status, medication use, intervention dose (servings/day), and baseline level of the end value. Sensitivity analyses will include completers, per protocol analyses, and ITT with MI.

Prespecified subgroup analyses will be conducted using Chi-square tests by age, sex, NAFLD status, caffeinated beverage use (cola vs non-cola drinkers), intervention dose (servings/day), and baseline waist circumference, FPG, 2hPG, Triglycerides, HDL-C, BP. Continuous linear (dose response gradient) and non-linear (dose response threshold) dose-response analyses will be undertaken over the natural dose response range (3, 4, 5, or 6 servings per day) by multiple linear regression and piecewise regression analyses, respectively.

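### Entry requires neither metabolic syndrome nor a measured absence of diabetes, and the MetS reversion and diabetes incidence outcomes state no week 0 risk set

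*Protocol*

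**What the plan says.** **Population.** The Protocol Summary gives the study population as "Overweight/obese participants with MetS who are consuming" at least one sugar-sweetened beverage (SSB) a day. Nearly every objective in Table 1 repeats the MetS qualifier; the adherence objective is the exception. Section 4.1 describes the same trial without it: "established cardiometabolic risk factors in overweight/obese participants who are consuming" SSBs.

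**Eligibility.** Section 5.1 opens with "In order to be eligible to participate in this study, an individual must meet all of the following criteria" and lists age, BMI, waist circumference and SSB intake. Section 5.2 excludes "Self-reported diabetes" and adds the general note that "Disease exclusions will be based upon self-reported diagnosis".

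**Measurement before randomisation.** The in-person screening in Section 4.5 takes height, weight, waist and blood pressure. Table 4 shows no blood sample at screening or run-in. The first fasting bloods and oral glucose tolerance test (OGTT) are at week 0.

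**Outcomes.** Section 7.3 defines MetS reversion as "Reversion to <3 of 5 IDF/NHLBI/AHA/WHF/IAAS/IASO MetS criteria measured at weeks 0 and 24", with the end value at week 24, and diabetes as "Incidence of diabetes (Diabetes Canada 2018 FPG and 2h-PG [75g-OGTT], or HbA1c criteria) measured at week 24".

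**Analysis.** Section 11 analyses these outcomes by intention to treat with inverse probability weighting. It uses logistic regression for categorical data, reporting "odds ratio with 95% CI for MetS reversion and relative risk with 95% CI for diabetes incidence", and adjusts for the baseline level among other covariates.

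**The concern.** A reversion can occur only in someone who has the condition at baseline, and an incident case only in someone who does not. The entry criteria secure neither state, and no other text fixes the set of participants at risk.

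Two things are at stake. First, the event counts and the effect estimates built on them would mix true transitions with states already present at week 0. Randomisation balances such participants across arms in expectation, so the likely result is dilution towards no effect and not bias in favour of one arm. Second, conclusions would be stated for a MetS population that the trial did not require at entry.

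**Working it through.** **Step 1: do the entry rules secure the baseline states?**

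| MetS component | Required by Section 5.1? | First measured |
|---|---|---|
| Waist circumference | Yes | Screening |
| Blood pressure | No | Screening |
| Fasting glucose | No | Week 0 |
| Triglycerides | No | Week 0 |
| HDL-C | No | Week 0 |

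One of five components is guaranteed, and MetS needs at least two more. Under Section 4.5, eligibility is settled before the four-week run-in, so before any blood is drawn. No text uses week 0 results to confirm MetS or exclude diabetes.

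**Step 2: do the outcome definitions supply the missing restriction?** For diabetes they do not: the outcome is measured at week 24 only. For MetS the week 0 measurement is mentioned, but a requirement of at least 3 criteria at week 0 is not stated. The analysis set in Section 11 is not restricted by baseline status for either outcome.

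**Step 3: illustrative size for MetS reversion.** The Protocol gives no figure for either outcome, so there is none to reproduce and every input here is an assumption. Let q be the share without MetS at week 0 (20% or 50%). Of these, 90% are below 3 criteria at week 24 in both arms. True reversion among those with MetS is 30% (milk arm) versus 15% (SSB arm).

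True OR = (0.30/0.70)/(0.15/0.85) = 2.43.

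Observed rate = q × 0.90 + (1 − q) × r, where r is the true reversion rate.

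- q = 0.20: 0.18 + 0.24 = 0.42 versus 0.18 + 0.12 = 0.30. Crude OR = (0.42/0.58)/(0.30/0.70) = 1.69.
- q = 0.50: 0.45 + 0.15 = 0.60 versus 0.45 + 0.075 = 0.525. Crude OR = (0.60/0.40)/(0.525/0.475) = 1.36.

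Share of counted reverters who never had MetS: 0.18/0.42 = 43% and 0.18/0.30 = 60% at q = 0.20; 0.45/0.60 = 75% and 0.45/0.525 = 86% at q = 0.50.

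**Step 4: the same with baseline MetS status as the adjustment covariate.** The Mantel-Haenszel OR over the two baseline strata (OR 1 in the stratum without MetS) is [(1 − q) × 0.30 × 0.85 + q × 0.90 × 0.10] / [(1 − q) × 0.15 × 0.70 + q × 0.90 × 0.10].

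- q = 0.20: (0.204 + 0.018)/(0.084 + 0.018) = 0.222/0.102 = 2.18.
- q = 0.50: (0.1275 + 0.045)/(0.0525 + 0.045) = 0.1725/0.0975 = 1.77.

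**Step 5: illustrative size for diabetes.** Assume true 24-week incidence of 1% versus 2% (RR 0.50), undetected diabetes at week 0 in a share d, and 80% of those still meeting the criteria at week 24. Observed risk = (1 − d) × true risk + 0.80 × d, without adjustment.

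| d | Cases at week 0 among 186 | Observed risks | Observed RR | Share of SSB-arm cases present at week 0 |
|---|---|---|---|---|
| 1% | 1.9 | 0.0179 vs 0.0278 | 0.64 | 0.008/0.0278 = 29% |
| 3% | 5.6 | 0.0337 vs 0.0434 | 0.78 | 0.024/0.0434 = 55% |
| 5% | 9.3 | 0.0495 vs 0.0590 | 0.84 | 0.040/0.0590 = 68% |

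**The case against.** **The outcome names imply the risk sets.** Reversion measured at weeks 0 and 24 can fairly be read as presupposing at least 3 criteria at week 0, and the Table 1 objective for it is set in people with MetS. This stands: a reader might infer that the Protocol decides to count never-MetS participants as reverted, and it does not say that. It leaves the point open. The argument is weaker for diabetes, where the word incidence implies new cases but the definition names only week 24.

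**Risk sets for exploratory outcomes can be left to a statistical analysis plan.** This is true as far as it goes. Such a plan could not, however, reconcile the stated population with the inclusion list, and the week 24 time point and the intention-to-treat set are stated in the Protocol itself.

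**The planned analysis adjusts for baseline.** This also stands. A reader might take the crude ORs of 1.69 to 1.36 as what the plan would report. Section 11 includes a baseline-level covariate. If that means MetS status, the attenuation is milder but still present, and the counts stay mislabelled. The form of the covariate is not specified. As defined, diabetes has no week 0 measurement to adjust for.

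**Logistic regression and the relative risk.** A reader might infer that the two are incompatible. They are not: a logistic model can yield a relative risk by standardisation. What is missing is how it would be obtained.

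**Conclusion.** The concern holds in this form. The stated population contradicts the inclusion list. Diabetes already present at week 0 would count as incident under the definition and analysis set as written, and this is the firmest part. MetS reversion has an unstated risk set that, read literally, admits participants who never had the syndrome.

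The true size is unknown. Under the assumptions above, a reversion OR of 2.43 would appear as 1.69 to 1.36 crude, or about 2.18 to 1.77 with baseline MetS status as covariate. A diabetes RR of 0.50 would appear as 0.64 to 0.84 unadjusted. These ranges rest on assumed rates, and on participants without MetS behaving alike in both arms.

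A reader might infer that the trial's main result is at risk; the documents do not support that. Both outcomes are in the other pre-specified tier, and the sample size rests on liver fat alone. This should be corrected, but it does not threaten the primary comparison.

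**What to change.** 1. Analyse MetS reversion only in participants with at least 3 of 5 criteria at week 0.
2. Analyse diabetes incidence only in participants who do not meet the diabetes criteria on week 0 tests: fasting and 2-hour glucose, plus HbA1c if measured then. HbA1c is listed as an assay in Section 8.2.2.2, but Table 4 does not name it at week 0.
3. Reword the Protocol Summary and the Table 1 objectives to match Section 5.1: overweight or obese, high waist circumference, regular SSB intake. Adding MetS as an entry criterion would also remove the contradiction. It would, however, need glucose and lipids before randomisation, hence a new screening blood test and more screen failures, so rewording is the cheaper course.
4. Minor: state how the diabetes relative risk is obtained, for example by standardisation from the logistic model or by modified Poisson regression, or report an odds ratio.

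Cost: a few sentences and smaller denominators for two outcomes. The glucose, lipid, waist and blood pressure data needed are already collected at week 0.

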## **8. PROCEDURES**

### **8.1. Compliance assessment**

To assess compliance, beverage logs will be checked at each visit. In addition, urinary analysis and blood analysis will be done (see adherence outcomes) at 3 time points: at the beginning (week 0), in the middle of the trial (week 12) and end of the trial (week 24).

### **8.2. Analytical techniques**

#### **8.2.1. Anthropometric and blood pressure analyses**

Height will be measured with a wall-mounted stadiometer (Perspective Enterprises, Portage, MI, USA). Body weight will be assessed by beam scale. Waist circumference will be assessed using the Heart and Stroke Foundation methodology [64]. Blood pressure (BP) and resting heart rate will be measured. To collect this measure, participants will remain seated in a quiet, temperature-controlled room for at least 5 minutes to achieve resting heart rate and BP. Subsequently, BP will be measured oscillometrically using the OMRON Intellisense HEM-907 according to JNC VII criteria. BP will be measured in triplicate, with each measurement separated by one minute, and the average of the three measures will be taken [65].

#### **8.2.2. Biochemical analyses**

The fecal microbiome analysis and the objective biomarkers of the beverage assays will be performed at the Department of Nutritional Sciences, University of Toronto; plasma glucose, plasma insulin, liver enzymes, inflammation marker, uric acid, lipid analyses and kidney function analyses will be performed at the Banting and Best Diabetes Center (BBDC), University of Toronto.

##### **8.2.2.1. Fecal microbiome analysis**

DNA will be extracted from fecal samples and compositional analysis will be done by next generation sequencing. Primers will be used to target the appropriate regions of the *16S rRNA* gene for pair-end sequencing using Illumina MiSeq [66]. Sequencing data will be analyzed to assign Operational Taxonomic Units (OTUs) to determine their abundance. Data for selected taxa will be confirmed by qPCR [67]. Alpha and beta diversity indexes will be calculated. The metagenome will be inferred from compositional data *in silico* [68].

##### **8.2.2.2. Plasma analyses**

Plasma samples for glucose and insulin will be separated by centrifuge and the plasma immediately frozen at  $-80^{\circ}\text{C}$  at the University of Toronto, in a locked room, in a locked building for analysis. The BBDC at the University of Toronto will perform analyses of the plasma glucose using the glucose oxidase

method [69] and plasma insulin using the Cobas Elecsys insulin assay (Roche Diagnostics GmbH, Mannheim, Germany), and of the serum liver enzymes (ALT, AST, GGT, ALP), inflammation marker (hs-CRP), uric acid, HbA1c and lipid analyses (Triglycerides, HDL-C, LDL-C, and total cholesterol). Plasma glucose and insulin curves will be plotted as the incremental change over time and iAUC will be calculated geometrically for each participant using the trapezoid method, ignoring areas below the fasting value [70]. Remaining samples will be stored at -80° C for future analysis of metabolomics. The Matsuda ISIOGTT will be calculated using the 75g-OGTT derived plasma glucose (PG) and insulin (PI) values, according to the formula by Matsuda et al. [34]: 10 000 divided by the square root of  $[(FPGFPI) \cdot ([\text{mean PG} - \text{mean PI}])]$ , where PG is expressed in mg/dl (0.0551mmol/L) and PI in U/ml (6pmol/L). The early insulin secretion index ( $\Delta PI_{30-0} / \Delta PG_{30-0}$ ) will be calculated as the change in PI from 0 minutes to 30 minutes divided by the change in PG over the same period [71].

